### Participants’ consent

One day prior to the surgical procedure, investigators [name] will perform eligibility screening on patients slated for elective arthroscopic shoulder surgery the subsequent day. For those patients who satisfy all the inclusion criteria and none of the exclusion criteria, the investigators will disclose the study-related details to the patients and their family members or legally authorized representatives in an easy-to-understand manner, with sufficient time reserved for the patients to ask questions and confirm details.

The disclosed information encompasses the study’s primary and secondary objectives, detailed procedural steps (including preoperative baseline measurement of diaphragmatic function and pulmonary function, ultrasound-guided subparaneural brachial plexus block at the upper trunk bifurcation, standardized general anesthesia management, and postoperative outcome assessment in the post-anesthesia care unit [PACU]), potential therapeutic benefits (effective postoperative pain control with reduced risk of hemidiaphragmatic paresis and respiratory-related complications), possible adverse events (including local anesthetic allergy, nerve injury, local anesthetic toxicity, intraoperative hypotension, postoperative nausea and vomiting, and other anesthesia-related complications), and corresponding risk-mitigation strategies. The investigators will also explicitly inform the patients that the study is for scientific research purposes only, and their participation will not incur any additional medical expenses beyond routine clinical treatment.

In the event that patients express their willingness to partake in the study after fully understanding all the above information, either they or their legally authorized representatives are required to sign the written informed consent form in triplicate. One copy of the signed form will be provided to the participant or their legal representative, one will be filed in the participant’s electronic medical record, and the third will be securely archived by the research team in the study-specific locked filing cabinet, in compliance with the requirements of the institutional ethics committee.

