### Randomization and blindness

#### Randomization procedure and allocation concealment

This study uses a blocked randomization design with a fixed block size of 4 to ensure a strict 1:1 allocation ratio throughout the entire recruitment process. This design guarantees that after every 4 subjects are enrolled, there will be exactly 2 subjects in each group, eliminating any risk of significant group imbalance even in the presence of dropouts. The randomization sequence was generated by [name] using R software (version 4.4.3) with a fixed random seed of 13,579 to guarantee full reproducibility of the allocation sequence. A total of 100 eligible patients will be randomly assigned to either the 2 mL 0.375% ropivacaine group or the 5 mL 0.375% ropivacaine group.

Allocation concealment was achieved using the sequentially numbered, opaque, sealed envelopes (SNOSE) method, which is the gold standard for allocation concealment in single-center clinical trials. Each random allocation result was recorded on a pre-printed card, which was then placed into an individual opaque, non-resealable envelope. The envelopes were numbered sequentially from 1 to 100 and sealed to prevent any prior tampering or detection of the allocation result.

[name], who generated the randomization sequence, has no involvement in patient recruitment, intervention implementation, outcome assessment, or data analysis. The sealed envelopes are stored in a locked filing cabinet with restricted access, and only [name], the dedicated anesthesiology nurse responsible for study drug preparation, has access to the envelopes. When a patient meets all inclusion criteria and provides written informed consent, [name] will open the next sequentially numbered envelope immediately before the nerve block procedure, prepare the study drug according to the allocation result, and record the envelope opening time and group assignment in a dedicated study log.

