### Baseline pulmonary function test and diaphragmatic excursion measurement

Subjects sign the written informed consent form one day before surgery, and remain fully blinded to their group allocation throughout the perioperative period. No premedication is administered to any subject in the ward before surgery.

On the day of elective surgery, all subjects follow the standard preoperative fasting protocol, with 8 h of fasting for solid food and 2 h of fasting for clear liquids. After entering the operating room, a peripheral venous access is established on the non-operative upper limb of each subject, followed by a rapid infusion of 8 mL/kg lactated Ringer’s solution over 15–20 min for initial volume expansion. For patients with a history of cardiovascular disease (including heart failure, coronary artery disease, or hypertension), the infusion rate and total volume will be individually adjusted based on clinical assessment to avoid volume overload. Standard non-invasive monitoring is initiated immediately, including continuous electrocardiogram (ECG), non-invasive blood pressure (NIBP), and pulse oxygen saturation (SpO₂). Baseline vital signs (heart rate, systolic blood pressure, diastolic blood pressure, mean arterial pressure, and SpO₂) are recorded before any anesthetic or study intervention, and all intraoperative vital signs are continuously documented in the electronic anesthesia record system throughout the procedure.

Immediately after the above preoperative preparation is completed and strictly before the implementation of the study intervention (ultrasound-guided subparaneural block at the brachial plexus upper trunk bifurcation), all baseline diaphragmatic excursion and pulmonary function measurements are performed. The core purpose of these measurements is to obtain paired baseline data for the primary and secondary endpoints of this patient- and outcome assessor-blinded randomized controlled trial, so as to evaluate the differences in diaphragmatic function and pulmonary function between the 2 mL and 5 mL 0.375% ropivacaine groups after the study intervention.

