For diaphragmatic excursion measurement, the anterior subcostal approach is adopted by [name], with the liver (for subjects undergoing right-sided shoulder surgery) or the spleen (for subjects undergoing left-sided shoulder surgery) used as the acoustic window. The measurement is performed using the SONOSITE SII® ultrasound system (FUJIFILM SonoSite, Inc., Bothell, USA) equipped with a low-frequency (1 to 5 MHz) convex array probe. After clearly visualizing the continuous diaphragmatic pleural line, the probe position and angle are fixed, and the system is switched to M-mode to record the waveform of diaphragmatic movement during deep breathing. Three stable and reproducible diaphragmatic movement waveforms during deep breathing are continuously recorded for each subject, the excursion amplitude (cm) of the ipsilateral hemidiaphragm is measured for each valid waveform, and the average value of the three measurements is calculated and documented as the baseline diaphragmatic excursion value of the subject. All original ultrasound images of the measurements are archived in real time for subsequent review and data verification.

For pulmonary function testing, [name] uses a CONTEC SP80B handheld spirometer (CONTEC Medical Systems Co., Ltd., Hebei, China) with the subject remaining in the same standardized semi-sitting position. The subject wears a nose clip and holds a disposable mouthpiece, and completes forced expiration maneuvers following standardized verbal instructions, in strict accordance with international pulmonary function testing guidelines. Three valid and reproducible forced expiration measurements are completed for each subject, with invalid curves (such as those caused by insufficient expiratory time, poor initial expiratory burst, or air leakage) excluded. The forced expiratory volume in 1 s (FEV1) and forced vital capacity (FVC) of each valid measurement are recorded, and the average value of the three valid measurements is calculated and documented as the baseline FEV1 and FVC values of the subject. The baseline FEV1/FVC ratio is calculated simultaneously, and subjects with a baseline FEV1/FVC < 70% are excluded from the trial in accordance with the pre-specified exclusion criteria.

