### Ultrasound-guided subparaneural block at the brachial plexus upper trunk bifurcation

All block procedures are independently performed in full by [name], a senior anesthesiologist with extensive experience in ultrasound-guided brachial plexus block, who has completed more than 200 standardized ultrasound-guided upper trunk block procedures prior to the trial. [name] is prohibited from participating in any baseline or postoperative outcome assessments, and only obtains the pre-prepared study drug corresponding to the subject’s enrollment number from [name], the dedicated anesthesiology nurse responsible for randomization management and study drug preparation, only after [name] has fully completed all baseline pulmonary function and diaphragmatic excursion measurements and archived the original data. [name] is only aware of the injection volume of the study drug for the individual enrolled subject, and is strictly prohibited from disclosing any allocation-related information to other study personnel, the subject, or the surgical team.

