The subject is placed in a standardized supine position, with the head gently rotated to the contralateral side of the surgery, and the operative upper limb kept in a neutral position without abduction throughout the procedure, to ensure stable visualization of the brachial plexus anatomical structure. The SONOSITE SII® ultrasound system (FUJIFILM SonoSite, Inc., Bothell, USA) equipped with a high-frequency (6 to 13 MHz) linear array ultrasound probe is used for pre-scanning of the target region, following a systematic anatomical localization strategy. Scanning is commenced from the neck region to accurately locate the transverse processes of the C5 to C7 cervical vertebrae and the corresponding nerve root exit sites via cross-sectional scanning; thereafter, the probe is moved distally along the course of the brachial plexus to the supraclavicular fossa region. During the scanning process, the convergence of the C5 and C6 anterior rami to form the upper trunk of the brachial plexus is clearly visualized, followed by the trifurcation of the upper trunk into the anterior division, posterior division, and suprascapular nerve at the bifurcation point in the supraclavicular fossa. The probe is slowly tilted, slid and rotated to adjust the ultrasound beam incident angle, to obtain the optimal ultrasound view where the anterior division, posterior division, and suprascapular nerve of the upper trunk are arranged in a triangular or linear pattern within the same intact paraneural sheath.

After obtaining the optimal ultrasound view, the puncture site is disinfected and sterile drapes are applied following routine clinical sterile requirements for regional anesthesia. Local infiltration anesthesia is performed at the puncture site with 1 mL of 1% lidocaine solution. A 22 G × 50 mm nerve block needle is connected to a syringe pre-filled with the study drug (0.375% ropivacaine, 2 mL for the intervention group and 5 mL for the control group, prepared by [name] in advance according to the randomization allocation). The in-plane technique is used for needle advancement, with the needle inserted from the lateral to medial direction at an angle of 30° to 45° relative to the skin (27, 28). The entire length of the needle shaft is continuously visualized under real-time ultrasound guidance throughout the advancement process.

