##### Definition of analysis populations

Three distinct analysis populations will be defined and used for different analytical purposes:

(1) Intention-to-Treat (ITT) population (primary analysis population)

The ITT population includes all randomized subjects who have received at least one dose of the study intervention (2 mL or 5 mL 0.375% ropivacaine). This population will be used for the primary analyses of both co-primary endpoints (analgesic efficacy non-inferiority and HDP incidence superiority), as it preserves the randomization-generated group balance and minimizes selection bias, providing the most conservative and generalizable results.

(2) Per-Protocol (PP) population (sensitivity analysis population)

The PP population includes subjects who strictly adhere to the study protocol and meet all of the following criteria:

Received the full assigned study intervention with no wrong-group medication administrationCompleted all primary outcome assessments (pre-rescue NRS pain score and diaphragmatic excursion measurement in the PACU)Had no major protocol violations that could impact the interpretation of primary outcomes, including:

Preoperative use of prohibited analgesic or sedative medicationsUnplanned additional local anesthetic administration during the procedureIncomplete blinding due to accidental disclosure of group allocationLoss to follow-up before completion of primary outcome assessments

The PP population will be used for sensitivity analyses to verify the robustness of the ITT results. If the ITT and PP analyses yield consistent conclusions, the primary findings will be considered robust.

3 Safety analysis population.

The safety analysis population includes all randomized subjects who have received at least one dose of the study intervention. This population will be used for all safety-related analyses, including the incidence of adverse events and serious adverse events.

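### The envelope is opened before the pre-scan that shows whether the block target can be seen, and the trigger sentence does not mention the exclusion criteria or baseline spirometry

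*Protocol article*

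**What the plan says.** **Screening.** *Participants' consent* places eligibility screening on the day before surgery. Study information is then given to "For those patients who satisfy all the inclusion criteria and none of the exclusion criteria".

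**Envelope.** Under *Randomization procedure and allocation concealment*, the condition is "When a patient meets all inclusion criteria and provides written informed consent". The nurse then "will open the next sequentially numbered envelope immediately before the nerve block procedure" and prepares the drug. The same section describes the 100 patients to be assigned as eligible.

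**Baseline.** Spirometry and the diaphragm scan are done in the operating room on the day of surgery, "strictly before the implementation of the study intervention". At that point "subjects with a baseline FEV1/FVC < 70% are excluded from the trial in accordance with the pre-specified exclusion criteria".

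**Drug handover.** The block section lets the operator receive the prepared drug only once the assessor "has fully completed all baseline pulmonary function and diaphragmatic excursion measurements and archived the original data".

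**Pre-scan.** In the same block section, a linear probe "is used for pre-scanning of the target region, following a systematic anatomical localization strategy". The aim is a view of the two divisions and the suprascapular nerve inside one sheath. Disinfection and connection of the pre-filled syringe come next, and the syringe has been made up beforehand according to the allocation.

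**Who knows the allocation.** *Blinding procedures* names two people: the nurse and the anesthesiologist who performs the block.

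**Primary analysis set.** *Definition of analysis populations* states: "The ITT population includes all randomized subjects who have received at least one dose of the study intervention". *Handling of study withdrawals* instead puts every randomized subject in the primary ITT analysis, whether or not the study is completed.

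**The concern.** Concealment should last until the final decision on whether a patient enters the trial. Restricting the primary set to treated patients is usually defensible when the decision to treat is made blind to arm. Here the last look at whether the block is feasible comes after allocation and belongs to someone who knows the arm. A patient not injected at that stage would leave the primary set through an unblinded judgment. Difficult anatomy could plausibly bear on both pain and drug spread, which are the two co-primary outcomes.

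There is also a drafting gap. The trigger names inclusion criteria and consent only, and the day-before screen asks for the absence of every exclusion criterion, although the study spirometry behind one of them is done the next day.

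**Working it through.** **1. Order of steps, from the sections read together**

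| Step | When | Relative to the envelope |
|---|---|---|
| Inclusion and exclusion screening, consent | Day before surgery | Before |
| Spirometry, FEV1/FVC exclusion, diaphragm scan | Operating room, before the intervention | Before, by inference |
| Envelope opened, drug prepared | Just before the block | – |
| Drug released to operator | Not until baseline data are archived | After |
| Pre-scan of the target | Within the block procedure | After |
| Needle and injection | Within the block procedure | After |

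The second row is an inference because the explicit baseline gate is on drug handover, not on the envelope. Since opening is tied to the moment before the block and spirometry precedes the block, the inference is strong. Only wording is at fault there. The pre-scan row is different: nothing in the article places the pre-scan before allocation.

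**2. What happens to a randomized patient who is not injected**

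- *Definition of analysis populations*: no dose received, so not in the primary set.
- *Handling of study withdrawals*: randomized, so in the primary set.
- Replacement is also unsettled if such a patient counts as withdrawn. *Handling of study withdrawals* allows no replacement. *Final sample size determination* replaces anyone who withdraws before completing the primary assessments.

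**3. Size: the plan's own figures**

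- Non-inferiority: n = 2(1.96 + 0.84)² × 1.6² / 1² = 2 × 7.84 × 2.56 = 40.14 per group (plan: 40).
- HDP: n = 7.84 × (1/6 × 5/6) / (1/6)² = 39.2, rounded up to 40 (plan: 40).
- Dropout: 40 / (1 − 0.2) = 50 per group, 100 in total (plan: 100). The allowance is 50 × 0.2 = 10 per group.

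The plan's figures are reproduced to within rounding. No rate of failed views is given, so no reduced sample size can be derived. A few such patients would fit within the 10 per group.

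**4. Size: sensitivity of the HDP criterion to single patients**

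The criterion under *Analysis of primary outcomes* is a lower one-sided 97.5% bound above 0 for the risk difference (5 mL minus 2 mL). With the unpooled standard error, the bound is RD − 1.96 × √[p₁(1−p₁)/n₁ + p₂(1−p₂)/n₂]. The plan's assumed rate gives 40 × 0.166667 = 6.7 expected events in the 5 mL group at 40 per group, and 50 × 0.166667 = 8.3 at 50 per group.

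- 5/40 v 0/40: 0.125 − 1.96 × 0.0523 = +0.022. Criterion met.
- 5/40 v 1/40: 0.100 − 1.96 × 0.0578 = −0.013. Criterion not met.
- 6/48 v 0/50, which is 8/50 v 0/50 with two 5 mL cases removed: 0.125 − 1.96 × 0.0477 = +0.031. Criterion still met.

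A single event can therefore matter when counts are near the boundary, but the loss of two events from about the expected count does not reverse the result. These counts are illustrations, not forecasts.

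**The case against.** A reader might infer that the exclusion criteria are not required before randomization, or that patients with FEV1/FVC below 70% are randomized and then removed. The documents do not support this. Screening demands that no exclusion criterion is present, both *Subjects and setting* and the randomization section speak of eligible patients being assigned, and spirometry with its exclusion comes before the block while the envelope is tied to the block. That objection stands in full and reduces this part to wording.

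On the pre-scan the opposing case has four parts.

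- No sentence gives the operator discretion to withhold the injection. The text tells the operator to adjust the probe until the optimal view is obtained, and more than 200 previous blocks are required. This stands: failed views are probably rare.
- A rule for failed visualization may be in the full protocol, which is not shown. This also stands, so the absence of such a rule is not the finding. The finding is the order of steps that the article does state.
- The article does not say that the operator already knows the volume while scanning, since the syringe is connected afterwards. This is correct, but nothing keeps the volume unknown until the view has been accepted, and the drug has been prepared beforehand.
- The operator cannot foresee HDP before injecting and so could not pick out future cases. This stands and limits the likely bias.

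The retention of all randomized subjects under *Handling of study withdrawals* does not rescue the plan, because the statistical section's own definition excludes the undosed patient.

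**Conclusion.** The point holds in a limited form. On the order written, allocation precedes the pre-scan, adequacy of the view is judged by the one operator who knows the volume, and the two statements of the ITT set disagree about a patient who is then not injected. The trigger sentence and the day-before screening sentence need tightening, but they do not show that ineligible patients are randomized.

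The effect is probably small. It depends on how often the view fails, which the documents do not state, and on a decision not to inject, which they do not describe. A reader might go on to infer a loss of power or deliberate selection by the operator. Neither is supported: no rate is available, the 20% allowance could absorb a few cases, and HDP is unknown before injection. The case for change is that a possible post-allocation exclusion by an unblinded person can be removed at very little cost.

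**What to change.** 1. In *Randomization procedure and allocation concealment*, state that the next envelope is opened only after (a) baseline spirometry and the diaphragm scan are complete and archived, (b) the absence of every exclusion criterion, including FEV1/FVC below 70%, is signed off, and (c) the operator, still unaware of allocation, has completed the existing pre-scan and recorded the view as adequate.
2. Log any failure before that point as a screen failure that uses no envelope.
3. In *Participants' consent*, limit the day-before check to exclusion criteria that can be assessed at that visit.
4. Reconcile *Handling of study withdrawals* with *Definition of analysis populations* for any randomized patient who is not injected, and settle in the same edit whether such a patient is replaced.

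What counts as an adequate view, and how a patient without one is managed, is for the investigators to set. The change concerns only when allocation is revealed.

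**Cost.** Existing steps are re-ordered and a short checklist is added, with no new procedure or staff. The downside is a few extra minutes in the operating room while the syringe is prepared after the pre-scan.

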#### Unblinding procedures

Formal final unblinding of the entire study will only be performed after complete database locking (all outcome data have been collected, verified, and frozen with no further modifications permitted) and finalization of the pre-specified statistical analysis plan. The unblinding ceremony will be conducted in the presence of the independent Data Monitoring Committee (DMC), principal investigator [name], independent statistician, [name], and a representative of the institutional Ethics Committee.

Unblinding is permitted only when it is absolutely essential to know the group allocation for the emergency treatment of the subject, such as the occurrence of life-threatening adverse events judged to be related to the study drug. The unblinding process is to be carried out exclusively by the principal investigator [name], with [name] required to provide the original envelope allocation record for verification. A detailed written record of the reason for unblinding, time, subject information, and group allocation must be made immediately by the principal investigator and filed with the nurse’s original records. The event and unblinding details must be reported to the institutional Ethics Committee within 24 h. All other investigators and study personnel are expected to maintain the blinded state to the greatest extent possible, and the unblinded subject will be excluded from the per-protocol (PP) analysis set, while retained in the intention-to-treat (ITT) analysis set as the primary analysis population of the trial.

